**LABORATORY MODELS OF COCAINE SELF ADMINISTRATION**

**Study Design Overview**

We propose to investigate effects of disulfiram 250mg compared to placebo on cocaine self-administration using a human laboratory model established by a group at Johns Hopkins ([name]). This investigator has agreed to serve as a consultant for this project, ensuring that the procedures followed are appropriate and that interpretation of the data is consistent with prior studies. Letters from the consultants are included in the appendix

Participants will be admitted to the hospital for 2 study visits. The visits follow the same layout, and participants will receive study drug during one visit and placebo during the other. Participants will be admitted to the hospital and will be randomized to study drug or placebo on the following day. During the next several days staff will familiarize participants with upcoming procedures and participants will complete a mock version study procedures. Participants will remain seated during experimental sessions except for brief visits to the lavatory. The first 30-min of all sessions will be devoted to the collection of baseline data and participant preparation.

At 1pm on days 5 and 7, participants will choose between a dose of cocaine (0mg or 20mg) or a monetary alternative in each of 10 subsequent choices. The same dose of cocaine, 0mg or 20mg, will be available for all 10 choices on a given day and each dose will be assigned to either day 5 or 7 in a randomized, double-blind manner. The monetary alternative will be $.05, $.05, $.05, $.05,$1, $4, $7, $10, $13, or $16 cash, presented in that order. Selections will be made at 15-minute intervals, and participants will receive cocaine doses or cash immediately after indicating their choice, providing vital signs remain within preset intervals. Heart rate variability measures will be conducted throughout the choice session as well.

Study drug will be discontinued on day 7, after completion of the experimental sessions. On day 8, the neurocognitive assessment and continuous heart rate recording will be repeated (as on days 1 and 4), starting at 3:00 PM. Again, subjects will be asked to refrain from smoking tobacco for at least 2 hours before the assessment.

Subjects will be monitored through day 8 and on day 9 they can either go home and return to complete the procedures under the alternate condition (placebo vs. disulfiram), or they can stay in the hospital and start the alternate study drug on the next day.

Subjects can be re-admitted to the study after several days or weeks and the experiment will be repeated during treatment with the alternate study drug (placebo or disulfiram). The total possible dose of cocaine that a patient can receive during choice sessions is 200mg, and the total dose they can receive over the study visit is 200mg.

In both studies, the participants will respond by pressing a response button or lever, depending on whether the patient controlled analgesia (PCA) pump or the Med Associates device incorporating FDA-approved Baxter infusion pump is utilized. When money choices have been selected, cocaine choices are unavailable for the remainder to the time-out period. For the purpose of these studies, the devices are interchangeable.

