7. Have a baseline ECG that demonstrates normal sinus rhythm, normal conduction, and no clinically significant arrhythmias; and
8. Have a medical history and brief physical examination demonstrating no clinically significant contraindications for study participation, in the judgment of the admitting physician and the principal investigator.

*Exclusion Criteria*

Potential participants will be excluded from participation in the study if any of the following apply:

1. Have any history or evidence suggestive of seizures or brain injury
2. Have any previous medically adverse reaction to cocaine, including loss of consciousness, chest pain, or epileptic seizure;
3. Have neurological or psychiatric disorders, such as:

- psychosis, bipolar illness or major depression as assessed by MINI (or SCID if necessary);
- organic brain disease or dementia assessed by clinical interview;
- history of any psychiatric disorder which would require ongoing treatment or which would make study compliance difficult;
- history of suicide attempts within the past three months assessed by MINI and/or current suicidal ideation/plan as assessed by MINI;

1. Have evidence of clinically significant heart disease or hypertension, as determined by the PI;
2. Have a family history in first degree relatives of early cardiovascular morbidity or mortality, as determined by the PI;
3. Have evidence of untreated or unstable medical illness including: neuroendocrine, autoimmune, renal, hepatic, or active infectious disease;
4. Have HIV *and* are currently symptomatic, have a diagnosis of AIDS, or are receiving antiretroviral medication;
5. Be pregnant or nursing. Other females must either be unable to conceive (i.e., surgically sterilized, sterile, or post-menopausal) or be using a reliable form of contraception (e.g., abstinence, birth control pills, intrauterine device, condoms, or spermicide). All females must provide negative pregnancy urine tests before study entry, upon hospital admission, and at the end of study participation;
6. Have any history of asthma, chronic coughing and wheezing, or other respiratory illnesses;
7. Currently use alpha or beta agonists, theophylline, or other sympathomimetics;
8. Currently meet criteria for alcohol dependence or refuse to abstain from alcohol during the protocol and for at least one week after discharge.

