##### *Criteria for Discontinuation Following Initiation*

1. positive urine toxicology or breath test indicating illicit use of cocaine, amphetamine, alcohol, opiates, or other abused drugs not delivered as part of this protocol;
2. inability to comply with study procedures;
3. meet discontinuation criteria due to exaggerated response to cocaine, described below.

*Rationale for Subject Selection Criteria*

Participants are required to have used cocaine by the IV or smoked route to avoid exposing participants to routes of administration that produce more intensive interceptive effects. The age criteria were selected primarily to avoid enrolling participants with undiagnosed cardiovascular disease. Participants with active HIV disease are excluded to avoid potential exacerbation of their underlying disease; participants with asymptomatic HIV are included because this group is at high risk for cocaine dependence. Participants with asthma (or who take asthma medications) are excluded due to potential adverse interactions between beta agonist medications and cocaine. Patients who heavily use alcohol are excluded due to the potential for disulfiram-alcohol reaction in the several days following completion of the protocol.

*Rationale for genetic assessments.* Data provided by [name] from an ongoing clinical trial shows that disulfiram was superior to placebo on both reported use and positive urine toxicology in patients with the DBH T allele (associated with lower enzyme activity), whereas in patients without the T allele disulfiram was superior to placebo only on reported use measures. Presumably, patients with the T allele have lower baseline DBH activity, and this is more sensitive to inhibition by disulfiram. We elected to allow participants with all DBH genotypes but test for DBH and COMT genotypes and to preferentially include patients with the C/T genotype in an effort to collect data from those most likely to respond to the medication. We will attempt to genotype participants before admission into the GCRC so that beds can preferentially be given to participants with the C/T genotype. Those with the C/C genotype will be enrolled when there is space available.

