**Protocols and Procedures**

Participants will reside as inpatients in the Clinical Research Center for the duration of this study. Participants will be required to refrain from illicit and prescription drug use for the duration of the study and this will be confirmed with daily urine and breath alcohol level testing. Caffeine and food will be prohibited during and 1-2 hours before study sessions.

Experimental sessions will be conducted at approximately the same time of day for a given participant. Experimental sessions will be several hours in duration and will be conducted in a quiet room on the GCRC with research and medical staff present. The room will contain an experimental station, equipped with a response console attached to a personal computer and video monitor. Participants will register selections by pressing a key on the response console. Heart rate, EKG, and blood pressure will be recorded throughout experimental sessions using a Scout automatic monitoring system. Medical personnel will monitor cardiac function during drug administration periods and for 2 hours following drug administration.

Participants will be admitted to the hospital and will be randomized to study drug or placebo on the following day. During the next several days staff will familiarize participants with upcoming procedures and participants will complete a mock version study procedures. Participants will remain seated during experimental sessions except for brief visits to the lavatory. The first 30-min of all sessions will be devoted to the collection of baseline data and participant preparation.

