**Experiments**

We propose assess effects of disulfiram and placebo on cocaine self-administration using an established laboratory model. Each participant will complete the experiment during treatment with placebo and disulfiram. The order in which a participant will receive disulfiram or placebo will be randomized to control for order effects.

At 1pm on days 5 and 7, participants will choose between a dose of cocaine (0mg or 20mg) or a monetary alternative in each of 10 subsequent choices. The same dose of cocaine, 0mg or 20mg, will be available for all 10 choices on a given day and each dose will be assigned to either day 5 or 7 in a randomized, double-blind manner. The monetary alternative will be $.05, $.05, $.05, $.05,$1, $4, $7, $10, $13, or $16 cash, presented in that order. Selections will be made at 15-minute intervals, and participants will receive cocaine doses or cash immediately after indicating their choice, providing vital signs remain within preset intervals. Heart rate variability measures will be conducted throughout the choice session as well.

Study drug will be discontinued on day 7, after completion of the experimental sessions. On days 1, 4 and 8, neurocognitive assessments and continous heart rate recording will be completed starting at 3:00 PM. Subjects will be asked to refrain from smoking tobacco for at least 2 hours before the assessment.

Subjects will be monitored through day 8 and on day 9 they can either go home and return to complete the procedures under the alternate condition (placebo vs. disulfiram), or they can stay in the hospital and start the alternate study drug on the next day.

Day 1 Admit to the CRC, complete neurocognitive testing with continuous heart rate recording.

Day 2 *Randomize to study drug 1. The order in*

which participants *receive disulfiram*

*and placebo will be randomized*

Day 3

Day 4 Neurocognitive testing with continuous heart rate recording.

Day 5 Choice session 1

*Participants will choose between cocaine (0mg or 20mg) and money*

Day 6

Day 7 Choice session 2

*Participants will choose between cocaine (0mg or 20mg, reverse of day 5) and money*

Day 8 Monitor. Neurocognitive assessment with continuous heart rate recording.

Day 9 Discharge or subjects can remain in hospital for study part 2

The total possible dose that a patient can receive during choice sessions is 200mg, and the total dose they can receive over the study visit is 200mg.

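### No minimum interval is set between the two study drugs, so placebo sessions can fall 6 and 8 days after the last disulfiram dose, and the rules for time at home between visits conflict

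*Protocol*

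**What the plan says.** The trial is a two-period crossover of disulfiram and placebo in randomised order. Within each visit, drug starts the day after admission. Protocol, Study Design Overview, fixes the sessions, "At 1pm on days 5 and 7, participants will choose between a dose of cocaine", and the end of dosing: "Study drug will be discontinued on day 7, after completion of the experimental sessions". The day list under Experiments ends: "Day 9 Discharge or subjects can remain in hospital for study part 2". A participant may go home and be readmitted days to weeks later, "or they can stay in the hospital and start the alternate study drug on the next day". No minimum interval appears anywhere.

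Three other places bear on this:

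- **Alcohol.** The Exclusion Criteria bar those who "refuse to abstain from alcohol during the protocol and for at least one week after discharge". The Rationale for Subject Selection Criteria excludes heavy alcohol users because of the "potential for disulfiram-alcohol reaction in the several days following completion of the protocol".
- **Time at home.** Protocols and Procedures says: "Participants will reside as inpatients in the Clinical Research Center for the duration of this study". It also requires abstinence from illicit drugs throughout, checked by daily testing. The first item under Criteria for Discontinuation Following Initiation is "positive urine toxicology or breath test indicating illicit use of cocaine" or other abused drugs not given by the study. It states no exception for time between visits.
- **Analysis.** The power statement under Statistical Analysis assumes no order effects. If order effects are found, the primary analysis is done within each order.

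**The concern.** In a crossover, the placebo sessions of those who took disulfiram first estimate a placebo response only if disulfiram no longer acts. Here the gap is not fixed and is largely the participant's choice, so exposure to possible carry-over is self-selected and arises in one order only. Randomising the order balances period effects on average but does not prevent carry-over. At stake is the primary contrast, disulfiram against placebo on cocaine choices.

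The alternative route has its own difficulty. Participants are non-treatment-seekers who use cocaine at least weekly (Inclusion Criteria). If the urine rule is applied literally on return, second-visit data are lost mainly from those who spent time at home, which is a selective loss.

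**Working it through.** **1. Day count.** Inputs: last dose day 7; transition day 9; alternate drug the next day, day 10; drug starts on visit-day 2; sessions on visit-days 5 and 7.

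- Day 10 = second-visit day 2, so second-visit day k = study day 8 + k.
- Sessions: 8 + 5 = day 13 and 8 + 7 = day 15. Since the last dose: 13 − 7 = 6 days and 15 − 7 = 8 days.
- If day 10 is counted as second-visit day 1 instead, the sessions fall on days 14 and 16, which is 7 and 9 days after the last dose.
- Going home, readmitted day 12: sessions on days 16 and 18 (9 and 11 days). Readmitted day 16: days 20 and 22 (13 and 15 days).

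**2. Comparison with the alcohol precaution.** Discharge on day 9 is 2 days after the last dose. One further week gives 2 + 7 = 9 days after the last dose, as a minimum. The back-to-back sessions at 6 and 8 days lie inside that span. The 7 and 9 days of the alternative count do not go past it.

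**3. What the within-order fallback estimates.** Let τ be the drug effect (disulfiram minus placebo), π the period effect (second minus first) and λ the disulfiram carry-over into the placebo sessions.

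- Disulfiram first: expected difference = τ − π − λ.
- Placebo first: expected difference = τ + π.
- Average of the two orders: τ − λ/2.

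The placebo-first contrast is free of disulfiram carry-over but contains π. The disulfiram-first contrast contains both π and λ. Splitting by order therefore does not recover τ.

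**4. The plan's power figure.** Inputs from Statistical Analysis: N = 60, d = .33 (f about .17), correlation .5, two-tailed α = .05, stated power .80.

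- SD of the within-person difference = SD × √(2(1 − .5)) = SD, so the standardised difference is .33.
- Noncentrality = .33 × √60 = 2.56 on 59 df. Two-sided power = .71.
- Using f = .17 with two conditions gives .74; one-sided at .33 gives .81. A two-sided .80 needs a difference of .368.

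The stated .80 is thus not reproduced two-sided for two conditions. That is a separate matter, so both starting points are carried forward.

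**5. Illustration of dilution.** The documents give no carry-over size. Assume a share c of the effect persists in a proportion q of disulfiram-first participants, with equal numbers per order. Then λ = qcτ and the estimate is multiplied by 1 − qc/2.

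| q | c | Multiplier | Estimate from .33 | Power from d = .33 | Power from stated .80 |
|---|---|---|---|---|---|
| – | 0 | 1 | .33 | .71 | .80 |
| 1 | .25 | .875 | .29 | .60 | .69 |
| 1 | .5 | .75 | .25 | .47 | .56 |
| 1 | 1 | .5 | .17 | .24 | .29 |
| .5 | .5 | .875 | .29 | .60 | .69 |

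If the residual effect had the opposite sign and half the size, the multiplier would be 1 + .25 = 1.25 and the estimate would be inflated to .33 × 1.25 = .41.

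**6. Time at home.** The Study Design Overview permits it. Protocols and Procedures, read as it stands, does not. The discontinuation criterion is silent on it. Stopping Criteria adds that participants must go on meeting the inclusion criteria, one of which is a cocaine-positive urine in the week of entry. The text does not say which of these governs a returning participant.

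**The case against.** **The alcohol window is not a cocaine-effect window.** It is a safety precaution that applies whichever drug came last, and someone who stays is not discharged on day 9. A reader might infer that the Protocol declares disulfiram still active on cocaine choice up to day 16. It does not: no passage gives a duration for any effect on cocaine choice. This objection stands. What remains is that the Protocol allows for residual disulfiram at about the relevant time and gives no reason why the placebo sessions would be unaffected.

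**The direction is open.** A reader might infer bias toward no effect. The disulfiram dose justification reports that 62.5 mg and 125 mg were associated with more cocaine use than placebo. If residual exposure acts like a low dose, the contrast could be inflated. This stands too, and the power figures above illustrate only one direction.

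**Going home does not breach the discontinuation rule.** A reader might infer that it does, but the rule needs a positive test. The text also speaks of separate visits, readmission and two parts, and daily testing is practicable only in hospital, so a per-admission reading is tenable. The conflict is therefore one of unclear scope, and data loss is a possible consequence only.

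**The Protocol does plan for order effects**, with a stated cost (f = .26, which gives power .79 at 30 per order and so reproduces). That is a fair point about precision, but step 3 shows the fallback does not isolate the drug effect.

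**The interval is not wholly the participant's choice**, because women's admissions are timed to the menstrual cycle. Hence the word largely.

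**Conclusion.** The concern holds in a limited form. The day count is firm: with no stated minimum interval, back-to-back participants who take disulfiram first have placebo sessions 6 and 8 days after the last dose (7 and 9 under the alternative count). That is a period in which the Protocol still guards against a disulfiram reaction. Carry-over onto cocaine choice is a reasonable inference, of unknown size and sign. The power statement assumes it away, and the fallback would not remove it.

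Under an assumed 50% persistence in all disulfiram-first participants, the estimate falls from .33 to about .25 SD and power from about .71 to .47 (.80 to .56 from the stated power). The loss is smaller if only some stay, and nil with no persistence.

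Separately, the passages on time at home conflict. Going home does not in itself lead to discontinuation, but a positive test on return would if the criterion is read literally, and the loss would be selective. This is a worthwhile and cheap correction. The documents do not show that the comparison is biased.

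**What to change.** - Reconcile the next-day start (Study Design Overview; Experiments) with the residual-reaction concern (Exclusion Criteria; Rationale for Subject Selection Criteria). Make the interval rule the same for both orders instead of leaving it to the participant. Its length is for the responsible clinicians and is not proposed here.
- State whether the first discontinuation criterion, the inpatient requirement and the abstinence requirement apply between visits or only during admissions, so that the Study Design Overview, the discontinuation criteria and Protocols and Procedures agree.
- Record the actual interval between the last dose of the first drug and the first dose of the second for every participant.
- Report the primary contrast by interval as a supportive sensitivity analysis. Where participants chose the interval it is a post-randomisation choice, so this cannot replace the design rule. The details may sit in the SAP.

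The cost is a small amendment, with a modest effect on retention and bed scheduling if some participants must wait or return. An interval that was not recorded may be hard to reconstruct later.

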**Research Participants**

Each subject will complete procedures while receiving placebo and disulfiram. We anticipate that 75 volunteers will enter the study and that there will be a dropout rate of 20-30%, yielding a sample size of 60.

*Recruitment*

Potential participants will be recruited using flyers, print ads, and radio advertisements. Our experience from previous studies indicates that well-placed and maintained flyers coupled with print and radio spots are sufficient to maintain frequent calls to our toll-free number. Over a recent 12-month period, our recruitment center received approximately 2,600 calls from stimulant users interested in participating in our studies. From those contacts, approximately 10% of the callers were eligible to meet with our research staff for consultation. Roughly 20% of those callers attended an initial screening appointment and met general inclusion criteria for a non-treatment-seeking study involving cocaine or methamphetamine administration (fewer met stricter criteria for particular studies, as some studies require prior IV experience). Thus, our existing recruitment approach provided about 50 eligible participants per year. We can easily increase the intensity of recruitment efforts in to accommodate the recruitment needs of the proposed project.

Participants who call our toll-free number are informed about the *general* requirements of the study and appointments are scheduled for those who are interested. Participants are not informed about the specific inclusion/exclusion criteria in order to avoid participants tailoring their responses in order to enter the protocol. During a face-to-face interview with a study physician participants are given consent documents that are read to them if needed. Following completion of the informed consent process, participants are screened using the criteria below. At several times during the screening process, participants are informed that treatment is available and referrals are provided if desired. Following completion of the consent process, participants will an oral swab will be used to collect epithelial cells that will provide DNA for genotyping at the DBH locus. Subjects with all genotypes will be included in this study.

*HIV issues.* After informed consent is obtained (described in *Human Subjects*), each participant will undergo HIV testing during their medical screening. A separate consent form for HIV testing provided by UCLA is signed and maintained in the patient’s clinical chart. In the event that any participant tests positive for HIV, he/she will be provided with counseling and medical follow-up. HIV itself is not exclusionary, though the presence of active disease is. Current use of antiretroviral medication is also exclusionary.

*Gender and race/ethnicity.* Participants will be selected without regard to gender or race/ethnicity. The estimates provided are based on our previous experience recruiting research volunteers. Due to the under-representation of women in drug abuse research, we will maximize recruitment of women by targeted advertising. Admission of women will be timed so that cocaine administration occurs during the follicular phase of the menstrual cycle, because cocaine plasma levels are greater then compared to the luteal phase (Lukas et al 1996).

*Participation of children.* Individuals under the age of 21 will not be excluded. Children younger than 18 years old will not be included in the proposed project because cocaine dependence (aside from abuse) is relatively rare in children under 18. The target population for this potential pharmacotherapy is cocaine-dependent adults, so participants for this study will sample from that population (see *Human Subjects*).

*Inclusion Criteria*

In order to participate in the study, participants *must*:

1. Be English-speaking volunteers who are not seeking treatment at the time of the study;
2. Be between 18-55 years of age;
3. Meet DSM IV criteria for cocaine dependence;
4. Have a self-reported history of using cocaine by the smoked or IV route. Participants must report at least weekly use for the past month and have a cocaine-positive urine test in the week of study entry;
5. Have vital signs after a 48 hours washout period as follows: resting pulse between 50 and 90 bpm, blood pressures between 85-150mm Hg systolic and 45-90mm Hg diastolic;
6. Have hematology and chemistry laboratory tests that are within normal (+/- 10%) limits with the following exceptions: a) liver function tests (total bilirubin, ALT, AST, and alkaline phosphatase) < 3 x the upper limit of normal, and b) kidney function tests (creatinine and BUN) < 2 x the upper limit of normal;
7. Have a baseline ECG that demonstrates normal sinus rhythm, normal conduction, and no clinically significant arrhythmias; and
8. Have a medical history and brief physical examination demonstrating no clinically significant contraindications for study participation, in the judgment of the admitting physician and the principal investigator.

*Exclusion Criteria*

Potential participants will be excluded from participation in the study if any of the following apply:

1. Have any history or evidence suggestive of seizures or brain injury
2. Have any previous medically adverse reaction to cocaine, including loss of consciousness, chest pain, or epileptic seizure;
3. Have neurological or psychiatric disorders, such as:

- psychosis, bipolar illness or major depression as assessed by MINI (or SCID if necessary);
- organic brain disease or dementia assessed by clinical interview;
- history of any psychiatric disorder which would require ongoing treatment or which would make study compliance difficult;
- history of suicide attempts within the past three months assessed by MINI and/or current suicidal ideation/plan as assessed by MINI;

1. Have evidence of clinically significant heart disease or hypertension, as determined by the PI;
2. Have a family history in first degree relatives of early cardiovascular morbidity or mortality, as determined by the PI;
3. Have evidence of untreated or unstable medical illness including: neuroendocrine, autoimmune, renal, hepatic, or active infectious disease;
4. Have HIV *and* are currently symptomatic, have a diagnosis of AIDS, or are receiving antiretroviral medication;
5. Be pregnant or nursing. Other females must either be unable to conceive (i.e., surgically sterilized, sterile, or post-menopausal) or be using a reliable form of contraception (e.g., abstinence, birth control pills, intrauterine device, condoms, or spermicide). All females must provide negative pregnancy urine tests before study entry, upon hospital admission, and at the end of study participation;
6. Have any history of asthma, chronic coughing and wheezing, or other respiratory illnesses;
7. Currently use alpha or beta agonists, theophylline, or other sympathomimetics;
8. Currently meet criteria for alcohol dependence or refuse to abstain from alcohol during the protocol and for at least one week after discharge.
9. Have any other illness, condition, or use of medications, which in the opinion of the PI and/or the admitting physician would preclude safe and/or successful completion of the study.

